#### Sampling method

This clinical trial has two intervention groups and one control group; each will be randomly (lottery) selected from a prenatal clinic and then samples will be selected based on convenience sampling method in clinics.

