### Phase III: Quantitative study

#### Type and direction of the quantitative study

The quantitative phase of the research will be implemented as a three-group semi-experimental study.

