#### Research environment

The research environment is three prenatal clinics which are affiliated to the Social Security Organization of Tabriz city. The reason for choosing such environment is the convenient access to pregnant women and their husbands in these settings and due to the fact that these centers have high daily attendance rates.

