#### Sample size

The sample size calculation is based on the results of previous studies, based on knowledge, attitude and practice variables using G-power software. The maximum sample size based on the practice variable and considering the data [power 95%, two sided α = 0.05, sd_2_ = 6.34, m_2_ = 88.81, sd_1_ = 14.69, m_1_ = 76.18] will be calculated with 22 people in each group, and due to probability of 10% loss, total sample size will be considered as 24. The final sample size will be determined based on the pilot study.

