#### Data analysis

The collected data will be analyzed using descriptive statistical methods (mean, standard deviation, minimum and maximum) and inferential statistics (One way analysis of variance, paired t-test, Chi-square, Fisher’s exact test, and Mann-Whitney) and by using SPSS 23 software.

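### Each Phase III arm is a single clinic, so the programme effect cannot be separated from clinic-specific change, and the stated 95% power and 5% alpha hold only if between-clinic variance is zero

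*Protocol article*

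**What the plan says.** All references are to Phase III of the protocol article.

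- **Type and direction of the quantitative study:** the phase is "implemented as a three-group semi-experimental study".
- **Research environment:** "The research environment is three prenatal clinics which are affiliated to the Social Security Organization of Tabriz city".
- **Sampling method:** the article states "This clinical trial has two intervention groups and one control group; each will be randomly (lottery) selected from a prenatal clinic". Within its clinic, each group is filled with couples taken by convenience. The only chance element mentioned is the lottery, and it is tied to clinics. No randomisation of couples is described.
- **Sample size:** the calculation uses "power 95%, two sided α = 0.05" and the practice score, with "sd_2_ = 6.34, m_2_ = 88.81" in one group and a mean of 76.18 (SD 14.69) in the other. It gives 22 per group, then 24 after 10% loss. The 24 is printed as a total, and the final size is left to a pilot study. No ICC or design effect appears.
- **Data analysis:** "One way analysis of variance, paired t-test, Chi-square", together with Fisher's exact and Mann-Whitney tests. No clinic term is named.
- **Data collection:** awareness, attitude and practice are measured before the intervention and 3 months after it. The implementation section confirms that this applies to intervention and control groups alike.

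**The concern.** Three groups and three clinics, with each group drawn from a clinic, make arm and clinic the same variable. The lottery decides which clinic receives which programme. With one clinic per arm it cannot balance the clinics' characteristics.

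A difference between arms at 3 months could come from the programme. It could also come from something that happened differently in one clinic over the same period, such as staffing, counselling practice or a local initiative. The couple-level tests count only the variation between couples within a clinic as error, so a real clinic difference reads as a programme effect.

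The stated Phase III objective is to determine the programme's effect, and the abstract says that an effective programme could enter perinatal care guidelines. A nominally significant result would carry that weight under an alpha and a power that the design does not guarantee.

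**Working it through.** **1. Reproduce the plan's figure.** Inputs are from the Sample size section.

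- Difference: 88.81 − 76.18 = 12.63.
- Pooled SD: √[(14.69² + 6.34²)/2] = 11.31.
- Standardised difference: 12.63/11.31 = 1.116.
- Two-sample t-test, two-sided 5%, 95% power: n = 21.86, so 22 per group. Power at 22 v 22 is 0.951.
- Loss: 22 × 1.1 = 24.2 and 22/0.9 = 24.4. The printed 24 therefore makes sense only per group.

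The stated 95% is thus the power of one pairwise comparison of 22 v 22 independent couples.

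**2. Count the allocated units.** Three clinics support three arm means, so 3 − 3 = 0 degrees of freedom remain for between-clinic variance. The data cannot estimate the ICC, and adding couples or fitting a mixed model does not change that.

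**3. Effect on the couple-level tests.** Let m = 22 couples per clinic and total variance σ².

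- True variance of an arm difference: 2σ²[ICC + (1 − ICC)/m].
- Variance that the test assumes: 2σ²(1 − ICC)/m.
- Ratio R = 1 + m·ICC/(1 − ICC). Standard errors are too small by a factor √R.
- Pairwise type I error: P(|t₄₂| > 2.018/√R).
- Three-group F-test type I error: P(F₂,₆₃ > F_crit/R).

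The ICC values are assumptions and refer to unadjusted outcomes.

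| Assumed ICC | R | √R | Pairwise type I | F-test type I |
|---|---|---|---|---|
| 0 | 1.00 | 1.00 | 5.0% | 5.0% |
| 0.01 | 1.22 | 1.11 | 7.5% | 8.4% |
| 0.02 | 1.45 | 1.20 | 10.1% | 12.3% |
| 0.05 | 2.16 | 1.47 | 17.7% | 24.1% |
| 0.10 | 3.44 | 1.86 | 28.3% | 40.7% |

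With 24 per clinic the picture is the same: 7.7% to 29.9% pairwise and 8.8% to 43.0% for the F-test.

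**4. Effect on power.** Suppose the ICC were known and allowed for. The design effect 1 + 21·ICC is then 1.21, 1.42, 2.05 and 3.10 for the four non-zero ICC values, and the effective n per arm is 18.2, 15.5, 10.7 and 7.1. Power by normal approximation is about 92%, 87%, 73% and 56%, against the stated 95%. These figures are optimistic, because the ICC is not known.

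**5. Compare the planned effect with plausible clinic noise.**

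- Between-clinic SD of an arm difference, √(2·ICC) × 11.31: 3.6 points at ICC 0.05 and 5.1 at 0.10. The planned 12.63 is 3.5 and 2.5 times these.
- Full standard error, 11.31 × √{2[ICC + (1 − ICC)/22]}: 4.9 and 6.0. The ratios to 12.63 are 2.6 and 2.1.

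**The case against.** **Baseline measurement.** Every outcome is measured before and after in all groups, and demographic and reproductive characteristics are collected. Stable differences between clinics, in catchment or education for example, can therefore be seen and adjusted for. A reader might infer that any clinic difference whatever is inseparable from the programme; the article does not support that. Two things remain. The Data analysis section does not say that the between-group comparison uses the baseline, and no baseline score removes change specific to one clinic.

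**Similar clinics and entry rule.** The clinics share a city and an organisation, and couples with earlier education on participation in perinatal care are not eligible. This makes a small ICC more plausible but does not establish zero.

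**Candid labelling.** Calling the study semi-experimental concedes that couples are not randomised. It does not tell the reader that each arm is one clinic, and the Sampling method section also speaks of a clinical trial with a lottery.

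**Contamination.** Separate sites are a recognisable way to keep arms of an educational programme apart, although the article does not give this reason. It is an argument for allocating clinics, not for one clinic per arm. It does count against insisting on within-clinic randomisation: the programme is not designed until Phase II, and any part acting on staff or clinic routine could not be allocated by couple.

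**An unanswerable question?** A reader might conclude that the data will be worthless. Step 5 shows otherwise: an effect of the planned size would still exceed the assumed clinic noise. The evidence is weaker and conditional on an assumption, not empty.

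**72 couples at 95% power?** A reader might multiply 24 by 3 and attach the power to that total. The article never prints 72, and the 95% belongs to a single two-group comparison.

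**Conclusion.** The point stands as a mismatch between the stated statistical properties and the design. With one clinic per arm, the programme effect cannot be separated from clinic-specific change over the follow-up, and the 95% power and 5% alpha apply only at ICC = 0.

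The size depends wholly on an ICC that the article does not give and the data cannot supply. Over the assumed 0.01 to 0.10, true type I error is about 7.5% to 28% pairwise and 8% to 41% for the F-test. Baseline adjustment may lower the relevant ICC, so the upper ends are high scenarios and not expected values.

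The conclusion also rests on reading the loosely worded lottery sentence as one clinic per group. That is the plain reading with three clinics and three groups.

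**What to change.** Before Phase III starts:

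- **Sample size section.** State that the 95% power (one comparison, 22 v 22) and the 5% alpha are conditional on no clinic effect, that is ICC = 0.
- **Data analysis section.** Compare arms on the 3-month outcome adjusted for its baseline value, to take out stable clinic differences in level. Report the contrasts again with standard errors multiplied by √[1 + m·ICC/(1 − ICC)] over a stated ICC range such as 0.01 to 0.10, as a sensitivity analysis.
- **Conclusions.** Limit them to a comparison of three clinics, attributable to the programme only if clinic-specific change is assumed negligible.

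These changes need no extra couples or measurements. They cost a wording amendment, a short additional analysis and a less favourable stated power.

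**Option to consider.** If the finished programme can be delivered couple by couple, run all three arms in every clinic. Randomise couples or recruitment weeks within clinic, and put clinic and any week-block in the model. This breaks the link between arm and clinic. It needs an amendment to the allocation paragraph, brings a risk of contamination within clinics, and may need more couples.

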#### Research sample

The research sample will be formed from the study population who entered the study with convenience sampling and have the inclusion criteria.

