#### The implementation method

The researcher will implement the proposed intervention after obtaining a permit from the Ethics Committee of Tabriz University of Medical Sciences and performing the necessary coordination with the designated centers’ officials. At first, through prenatal care records, the list of pregnant women with a gestational age of 20 to 22 weeks will be extracted and through phone, they will be invited together with their husband to participate in the research. After reaching the sample, knowledge and attitude of fathers in the intervention and control groups will be measured by questionnaires before intervention and their practice about participation in prenatal care will be measured by using questionnaire completed by their wives. After the implementation of the intervention program, the questionnaires will be completed again in the intervention and control groups.

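### Clinics are drawn to arms before couples are chosen by convenience and tested at baseline, with no concealment described, so recruitment and baseline answers can depend on the arm

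*Protocol article*

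**What the plan says.** All references are to Phase III of the protocol article.

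- **Sampling method.** The study has three groups: "This clinical trial has two intervention groups and one control group". A lottery ties each group to one clinic; after that comes the choice of couples, "and then samples will be selected based on convenience sampling method in clinics". The lottery comes first and the choice of couples second.
- **Research environment.** "The research environment is three prenatal clinics", so there is one clinic per group.
- **Research sample.** Convenience selection is repeated: participants are those who "entered the study with convenience sampling and have the inclusion criteria".
- **The implementation method.** The starting point is the clinics' files, from which "the list of pregnant women with a gestational age of 20 to 22 weeks will be extracted". Couples are then contacted: "through phone, they will be invited together with their husband to participate in the research". Baseline follows, in groups that already carry their labels: "After reaching the sample, knowledge and attitude of fathers in the intervention and control groups will be measured by questionnaires before intervention". Wives complete the practice questionnaire at the same point. The researcher delivers the programme.

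The article does not say who makes the calls, what they know of the lottery result, or in what order listed women are called.

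**The concern.** When whole clinics are allocated, the arm of every future participant in a clinic is fixed once the draw is made. If couples are recruited after that, randomising the clinics gives no protection against selective entry. Two features leave room for it here. Convenience sampling sets no rule for who is approached. One inclusion criterion, on harmony between the spouses, is a matter of judgement.

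The outcome makes this more serious than usual. The trial measures fathers' awareness, attitude and practice regarding participation, and a father's readiness to join in is closely related to that. If readiness affects entry differently by arm, the arms differ at the start on the outcome itself. Baseline answers given when the arm could be known may be affected too.

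The methods listed under Data analysis (one-way analysis of variance, paired t-test, chi-square, Fisher's exact and Mann-Whitney tests) include no between-arm comparison adjusted for baseline, so the named analysis would not offset such a difference.

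**Working it through.** **1. Order of events.** Sampling method puts the lottery before selection. The implementation method puts baseline after the sample is reached, in groups already named as intervention and control. The sequence is therefore lottery, convenience selection, baseline, programme. Three clinics for three groups means that knowing the clinic is enough to know the arm once the draw is known.

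**2. The plan's own sample size.** Inputs from Sample size: means 76.18 and 88.81, SDs 14.69 and 6.34, two-sided α = 0.05, power 95%.

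- Difference: 88.81 − 76.18 = 12.63.
- Root-mean-square SD: √[(14.69² + 6.34²)/2] = √[(215.80 + 40.20)/2] = 11.31.
- Standardised difference: 12.63/11.31 = 1.116.
- Normal approximation: n = 2(1.960 + 1.645)²/1.116² = 20.9, so 21 per group.
- Noncentral t: 22 per group, power 0.951. The stated 22 is reproduced.
- 10% loss: 22 × 1.1 = 24.2 or 22/0.9 = 24.4. This is 24 rounded down, as stated, or 25 rounded up.

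None of these inputs depends on when the lottery is drawn.

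**3. Size of the hazard.** The documents give no figure for a recruitment shift, so the following range is assumed.

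- 0.2 SD: 0.2 × 11.31 = 2.3 points; 2.3/12.63 = 18% of the planned difference.
- 0.4 SD: 0.4 × 11.31 = 4.5 points; 4.5/12.63 = 36%.

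**4. Effect on the false-positive rate.** Take two arms of 22, no true effect, a two-sided 5% t-test (42 degrees of freedom) on follow-up scores, and a shift of b SD carried in full to follow-up. The noncentrality is b/√(2/22).

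| Assumed shift (SD) | Points | Rejection rate |
|---|---|---|
| 0 | 0 | 5.0% |
| 0.1 | 1.1 | 6.2% |
| 0.2 | 2.3 | 9.9% |
| 0.3 | 3.4 | 16.3% |
| 0.5 | 5.7 | 36.7% |

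**5. What a later lottery would leave.** Drawing after baseline removes the part of the shift driven by knowledge of the arm. It does not remove ordinary differences between clinics. With one clinic per arm and an assumed intraclass correlation of 0.01, 0.02 or 0.05, the same test rejects in about 7.5%, 10% or 17.5% of trials with no true effect, whenever the draw is made.

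**The case against.** A reader might infer more than the article supports.

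- **That the caller knows the arm.** The article does not say who phones or what they know, and an article may leave that to the full protocol. This stands as a limit: knowledge of the arm is an inference. It is a strong one, because the clinic is the arm, the groups are named at baseline, the researcher delivers the programme and no concealment is described. The order itself is stated in the text and is not an omission.
- **That control couples receive a different invitation.** Only one invitation procedure is described, a phone call asking the couple to take part in the research. Different invitations by arm are possible but not stated.
- **That the bias must favour the programme.** This is likely if readier fathers enter the intervention arms, but not certain. Fathers who start high on a bounded scale have less room to improve, which could work the other way in change scores.
- **That the point range estimates the bias.** It is assumed. It also supposes that an entry difference carries over fully into an unadjusted follow-up comparison. All outcomes are measured before and after, so an imbalance would be visible, and within-group change is examined by paired t-test. Neither corrects the comparison between arms.

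It is also fair to say that convenience sampling is openly declared in a study labelled semi-experimental, and that the record list and a baseline before the programme are already planned. Both points bear on how little must change; neither removes the exposure created by drawing the lottery first.

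**Conclusion.** The concern holds in a limited form. As written, the plan permits recruitment and baseline answers to depend on the arm, and nothing described prevents it. The documents do not show that this will happen.

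The range of 2.3 to 4.5 points (18 to 36% of the planned difference) rests on an assumed shift of 0.2 to 0.4 SD, the planning SD of 11.31 and an unadjusted follow-up comparison. Within that range, a 0.2 SD shift would about double the nominal 5% error rate, to 9.9%.

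Two further readings should be resisted. Moving the lottery is not free, because all three clinics must finish before the draw while pregnancies advance from the 20 to 22 week entry. Nor would it make the arms comparable: clinic stays fully confounded with arm, and the exclusion of those who fail to receive 50% of the intervention can still select engaged fathers. Both are separate problems. The change is worth making because it removes one avoidable source of bias at small expense.

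**What to change.** Revise Sampling method, Research sample and The implementation method so that they give one sequence:

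1. In all three clinics, extract the list of eligible women and invite them in consecutive or random-number order, with one identical script. This replaces convenience sampling.
2. Obtain consent and complete all baseline questionnaires in all three clinics.
3. Only then draw the lottery that assigns clinics to arms.
4. Report the numbers invited and accepting in each clinic.

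**Cost.** There is no change to the sample size (22 per group, 24 with loss), the questionnaires or the number of measurements, since the plan already completes the sample and baseline before the programme. The downside is timing: the programme cannot start until the slowest clinic has finished enrolment and baseline. Enrolment should therefore run in parallel across the clinics over a short window, given the gestational-age entry criterion. The text should also say that this step does not address the confounding of clinic with arm or the 50% exclusion rule.

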#### The inclusion criteria

The inclusion criteria for this phase will include; being literate; not having passed any educational courses about participation in perinatal care; living harmoniously with spouse and without any challenge between couples.

#### Exclusion criteria

The exclusion criteria will include unwillingness to continue cooperation at each stage of the research and failure to receive 50% of the intervention for any reason.

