#### Objectives of the third phase: quantitative study

To determine the effect of the designed interventional program on awareness, attitude and practice of fathers about participation in perinatal care.

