#### Data collection

The tools used in the quantitative phase of this research are researcher-made questionnaires. The first part consists of demographic and reproductive characteristics; while the second part of the questionnaire is to assess the awareness, attitude and practice of fathers which will be completed before the intervention and 3 months after the intervention. The knowledge and attitude questionnaires will be completed by fathers and father’s practice questionnaire will be completed by their wives. The awareness questionnaire consists of 28 questions, which have three options: “correct”, “false” and “not sure.” The attitude questionnaire, which consists of 23 questions, is based on the Likert scale of 5 options with the answer “I totally agree”, “agree”, “do not comment”, “disagree”, and “completely disagree”. The practice questionnaire has 23 questions, based on the Likert scale, with the options “Never”, “rarely”, “sometimes”, “most often” and “always”.

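### The rule excluding couples who receive less than half of the intervention can act only in the two intervention groups and is likely to tilt the comparison towards the programme

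*Protocol article*

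**What the plan says.** All references are to Phase III of the protocol article.

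- **Exclusion criteria** gives two grounds: "unwillingness to continue cooperation at each stage of the research and failure to receive 50% of the intervention for any reason".
- **Sampling method** sets out the groups: "This clinical trial has two intervention groups and one control group; each will be randomly (lottery) selected from a prenatal clinic". Within each clinic, couples are recruited by convenience. No programme is described for the control group.
- **Objectives of the third phase** states the aim as "the effect of the designed interventional program on awareness, attitude and practice of fathers about participation in perinatal care".
- **Data collection** puts the outcome questionnaires at two times, "which will be completed before the intervention and 3 months after the intervention". Fathers complete awareness and attitude; wives complete practice.
- **The implementation method** adds: "After the implementation of the intervention program, the questionnaires will be completed again in the intervention and control groups".
- **Data analysis** lists "One way analysis of variance, paired t-test, Chi-square, Fisher’s exact test, and Mann-Whitney". It does not say who is analysed.
- **Sample size** uses "power 95%, two sided α = 0.05", with practice means 76.18 and 88.81 and SDs 14.69 and 6.34. It arrives at 22 per group, raised to 24 for 10% loss.

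**The concern.** Neither ground can be known when a couple enrols, so both work as removals after the groups have been formed. They differ in reach. Any couple in any group may stop cooperating. Only a couple who is offered a programme can receive less than half of it, so the second ground can never remove a control couple.

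The aim concerns fathers' participation in care. Fathers who take up little of a programme about participation are plausibly less engaged than the rest and may score lower at 3 months whatever the programme does. Their counterparts in the control clinic stay in. The comparison then sets a filtered intervention sample against an unfiltered control sample.

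At stake is whether the estimate describes the programme as offered to the couples enrolled. That matters because the abstract's Discussion proposes including the programme in perinatal care guidelines if it proves effective.

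This is not a complaint about detail left to a fuller document. The rule is written into the article, and nothing in the later Phase III sections offsets it.

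**Working it through.** **1. The plan's own figure.** Inputs are from Sample size.

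- Difference: 88.81 − 76.18 = 12.63 points.
- Common SD (root mean square): √((14.69² + 6.34²)/2) = √127.996 = 11.31.
- Standardised difference: 12.63/11.31 = 1.116.
- A two-sample t-test at two-sided 5% has power 0.942 with 21 per group and 0.951 with 22. The stated 22 is reproduced.
- Loss: 22 × 1.1 = 24.2, or 22/0.9 = 24.4. The stated 24, read as a per-group figure, is close to both.

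The calculation has no separate term for removal through low receipt of the programme.

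**2. Size of the bias when the programme does nothing.** Let *f* be the fraction of an intervention group removed by the 50% limb, and *g* the mean outcome of couples kept minus that of couples removed, in SD units. The full group's mean is (1 − *f*) × kept + *f* × removed, so the kept couples exceed it by *f* × *g*. With no true effect and otherwise comparable groups, that excess is the bias.

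The documents give neither *f* nor *g*. Assumed ranges are *f* = 10-20% and *g* = 0.5-1.0 SD.

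| *f* | *g* (SD) | Bias (SD) | Practice points (× 11.31) | Share of 12.63 |
|---|---|---|---|---|
| 0.10 | 0.5 | 0.05 | 0.6 | 4% |
| 0.10 | 1.0 | 0.10 | 1.1 | 9% |
| 0.20 | 0.5 | 0.10 | 1.1 | 9% |
| 0.20 | 1.0 | 0.20 | 2.3 | 18% |

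**3. Effect on type I error.** For one intervention group against control with 22 per group, the non-centrality is bias × √(22/2) = bias × 3.317. The rejection rate is P(|Z + non-centrality| > 1.96).

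- Bias 0.05: non-centrality 0.17, rate about 5.3%.
- Bias 0.10: non-centrality 0.33, rate about 6.3%.
- Bias 0.20: non-centrality 0.66, rate about 10%.

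With the listed three-group one-way ANOVA, 24 enrolled per group and both intervention groups shifted, the rates are about 5.3%, 6.1% and 9.5-9.7%.

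**4. A second selection model.** Suppose receipt and outcome are correlated with coefficient ρ and the lowest-receiving fraction *f* is removed from an intervention group only. The bias in SD units is ρ × φ(z_f)/(1 − *f*), where φ is the normal density and z_f the *f* quantile. Take ρ from 0.1 to 0.5, again an assumption, with 24 enrolled per group.

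| *f* | Bias (practice points) | Type I error at ρ = 0.5 |
|---|---|---|
| 0.10 | 0.22 to 1.10 | about 6% |
| 0.20 | 0.40 to 1.98 | about 9% |
| 0.30 | 0.56 to 2.81 | about 13% |

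The two models agree on the order of magnitude.

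**5. The loss margin.** The margin is 24 − 22 = 2 couples per group. Removing 10-20% of 24 takes 2.4 to 4.8 couples from an intervention group. The article does not define what the 10% covers, so whether these removals are included cannot be settled.

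**The case against.** Several counter-arguments have weight.

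- **The numbers are modest.** A reader might infer that the rule would make a useless programme show a benefit. The figures do not support that: in the worst assumed corner of the main range a null programme still fails to reach significance about 90% of the time, and the bias is at most about 18% of the planned difference. This stands.
- **Direction and size are assumed.** The article reports no level of receipt and no link between receipt and outcome. The rule applies whatever the reason, so it also covers causes unrelated to motivation. A reader might treat attendance as itself a form of the outcome, but practice is a 23-item questionnaire completed by wives, and the programme's format is left to Phase II. This stands: the direction is likely, not shown.
- **Half of the rule is ordinary withdrawal.** A reader might take the whole paragraph as one-sided. The cooperation limb can apply in all three groups, so the criticism is confined to the 50% limb.
- **Baseline is measured.** Outcomes are taken before the intervention in every group, and a paired test is listed. A pre-existing gap would partly cancel in change scores. This stands in part, since the article does not say that the between-group comparison is adjusted for baseline.
- **Couples are not randomised.** One clinic serves each group, with convenience samples inside it. True, but another weakness in the design is no reason to add an avoidable selection step.

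None of this gives a reason to keep the limb. It limits what can be claimed about its effect.

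**Conclusion.** The point holds for the 50% limb. It is a stated rule, applied after allocation, that can remove couples only from the two intervention groups, and the article does not say that they are followed up or analysed. The likely consequence is a small to moderate bias towards the programme. Under the main assumptions (10-20% removed, gap 0.5-1.0 SD, no baseline adjustment) it is 0.05-0.20 SD, or 0.6-2.3 practice points, with type I error between about 5.3% and 10%. Fewer removals or a smaller gap would bring it close to nil; the second model with 30% removed takes it to 2.8 points and 13%.

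Two further inferences should be resisted. The article does not show that poor uptake would be hidden, because it is simply silent on whether receipt will be reported. Nor would analysing everyone give a randomised comparison: group and clinic remain fully confounded with one clinic per group.

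**What to change.** 1. Delete under-receipt of the programme as an exclusion criterion.
2. Seek the 3-month questionnaires from every enrolled couple, however much of the programme they received, unless they refuse the questionnaires. Record stopping the programme separately from refusing further measurement. The wife-completed practice questionnaire can be collected even when the father has stopped taking part.
3. Make the main analysis all couples with outcome data, in the group assigned to their clinic.
4. Keep the 50% threshold only to define a secondary per-protocol analysis, and report receipt of the programme by arm.

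The cost is one reworded paragraph, a few more questionnaires and a possibly less favourable estimate. The calculated sample size does not change, because it contains no term for these exclusions. The change should be made before Phase III enrolment, since outcomes not collected from excluded couples cannot be recovered. It removes this one selection step and leaves the confounding of arm with clinic untouched.
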